**7. Trial schedule**

The prescribed observations and tests will be carried out according to the following schedule1. The patient will be hospitalized from before the first administration until the day after the administration.

For subjects in Phase Ia, the investigators will again obtain consent for the continuation of the trial prior to the fifth administration.

For subjects who have demonstrated a regulatory T-cell clearance effect and antigen-specific antibody immunoreactivity or SD or better on RECIST after 8 doses, maintenance administration of the investigational drug is allowed if the subject wishes to receive it and the investigators consider it appropriate to do so.

The date of the first dose of investigational drug is defined as 1 week.

Table 1. Clinical trial schedule

[figure not shown]

○：Additional items to be performed when maintenance dosing is performed after 8 doses.

*1: The ninth and subsequent doses of the investigational drug should be administered only when SD or better is confirmed in the regulatory T-cell elimination effect and antigen-specific antibody immunoreactivity or RECIST, the subject wishes to receive a maintenance dose of the investigational drug, and the investigator and others consider that the maintenance dose of the investigational drug is appropriate.

*2: Continuous observation from before the start to the end of study drug administration.

*3: To be conducted before administration of the investigational medicinal product during the period of administration of the investigational medicinal product.

*4: Before administration of the investigational drug, at 30 minutes, 1 hour, 1.5 hours after the start of administration, at the end of administration, 30 minutes and 1 hour after the end of administration.

*5: If it is difficult to collect the prescribed volume of blood due to signs of anemia, etc., the following tests should be performed in consideration of subject safety: 1. General blood test (facility prescribed volume), 2. Thyroid function test (facility prescribed volume), 3. Regulatory T cell test (10 mL), 4. Pharmacokinetic test (Phase Ia part only, 2 mL), 5. Antigen-specific antibody immunological reaction test (5mL), 6. Genetic analysis (15mL), 7. Immunopotentiation effect test (30~50mL), 8. Tumor markers (facility's specified volume), as much blood as possible in the order of priority.

*6: Testing is also performed at week 12 after the last dose of the study drug.

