**7-8. Maintenance dose implementation criteria**

If all of the following criteria are met, maintenance dosing of the investigational drug to the subject concerned will be permitted until "7-7-3.

1) Maintenance dosing can be started within 6 weeks after the 8 doses.

2) If the subject shows an SD or greater in regulatory T-cell elimination and antigen-specific antibody immunoreactivity or RECIST after treatment with the investigational drug.

3) The subject wishes to receive maintenance dosing of the investigational drug

4) The investigator determines that maintenance administration of the investigational drug is appropriate.

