**8-3-3. Other items defined**

1) Common to both Phase Ia and Phase Ib

(1) Antigen-specific antibody immunoreactivity test (NY-ESO-1 and XAGE-1b)

Antibody titers against NY-ESO-1 or XAGE antigens in serum are measured using recombinant NY-ESO-1 protein or synthetic XAGE protein by ELISA.

An IgG titer exceeding the mean of ELISA absorbance + 3 S.D. in healthy human serum is defined as positive, and an "increase" or "decrease" is defined as a change in the maximum dilution fold that shows positive results.

(2) Evaluation of regulatory T cells (optional)

Cell surface staining is performed using CD3, CD4, CD25, CD45RA, etc., which are markers of regulatory T cells. In addition, intracellular staining with transcription factor Foxp3, etc., and analysis using FCM. Among the regulatory T cells, the fraction with a strong inhibitory function that suppresses the anti-tumor immune response is accurately identified after careful removal of dead cells. Since this fraction strongly expresses CCR4, we will examine changes in this fraction upon administration of Mogamulizumab.

(3) Antigen-specific antibody immunoreactivity test (antigens other than NY-ESO-1 and XAGE-1b) (optional)

An ELISA using serum is performed to evaluate the enhancement effect of antigen-specific immune response. Measure the response to tumor antigens MAGE-A1, MAGE-A3, MAGE-A4, CT7/MAGEC1, CT10/MAGEC2, CT45, CT46/HORMAD1, SOX2, SSX2, p53 and other antigen proteins.

(4) Antigen-specific cellular immune response test (optional)

To evaluate the enhancement effect of antigen-specific immune response, antigen-specific CD4 and CD8 T cell responses are measured using peripheral blood. To observe the response to NY-ESO-1 and XAGE-1b, which are expressed 20-50% in the carcinoma of interest, CD4/CD8 T cells will be co-cultured with antigen-presenting cells to which NY-ESO-1 or XAGE-1b protein is added, and IFN-γ-producing cells will be detected by IFN-γ secretion assay.

(5) Evaluation of cytokine production (optional)

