**9-4. Efficacy parameters**

**9-4-1. Antigen-specific antibody immunoreaction tests (NY-ESO-1 and XAGE-1b)**

Blood samples will be drawn at baseline, every 4 weeks after 5, 9, and 12 weeks if possible, and every 4 weeks from the 9th dosing date for maintenance dosing, and at the time of discontinuation of the study, and measured by an external laboratory. However, on the day of administration of the investigational drug, blood should be drawn prior to administration of the investigational drug. If administration of the investigational drug is discontinued, blood should be drawn at the time of discontinuation of administration, and every 4 weeks after discontinuation if possible. Measurement results will be submitted directly to the data center from an external laboratory.

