**11-4. Analysis items and methods**

Detailed analysis methods are described in the "Statistical Analysis Plan" and "Pharmacokinetic Analysis Plan" to be prepared separately.

1) Safety

(1) Number of DLT cases

The number of DLTs and the incidence rate of DLTs per treatment group in Phase Ia are shown.

(2) Occurrence of adverse events and adverse reactions

Adverse events that occurred in Phase Ia and Phase Ib are summarized in the table. All adverse events and adverse drug reactions are summarized by the MedDRA basic terms and by major organ category, and the number and percentage of adverse events for each treatment group are shown.

(3) Gene analysis

Exploratory studies will be conducted as necessary.

2) Efficacy

(1) Efficacy in eliminating regulatory T cells

Summary statistics are calculated for each treatment group.

(2) Antigen-specific antibody immune response

To be investigated in an exploratory manner for each treatment group.

(3) Anti-tumor effect

The number of responders and the percentage of responders (response rate) will be calculated for each treatment group.

(4) Progression-free survival (PFS)

Progression-free survival is calculated using the Kaplan-Meier method.

(5) Overall survival (OS)

Overall survival is calculated using the Kaplan-Meier method.

(6) Immunostimulatory effect

To be examined on an exploratory basis as necessary.

(7) Gene analysis

To be explored as necessary.

In addition, the relationship between regulatory T-cell elimination effect and anti-tumor effect, antigen-specific antibody immune response, etc. will be explored.

3) Pharmacokinetics

(1) Plasma Mogamulizumab concentration

Plasma concentrations of Mogamulizumab will be listed and descriptive statistics for each dose will be shown; plasma concentration trends of Mogamulizumab will be plotted graphically as individual subject data and mean (+ standard deviation) versus blood collection time on a real and log scale.

(2) Mogamulizumab pharmacokinetic parameters

Calculate the pharmacokinetic parameters for each subject as indicated in "8-3-1 Definition of primary endpoints 1) Phase Ia Part (2) Pharmacokinetics" and calculate descriptive statistics for each dose.

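### The antibody rule in 8-3-3 (1) counts any one-step change in endpoint titre as an increase or decrease, so assay noise is reported as change in an exploratory immune result

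*Protocol*

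**What the plan says.** Protocol 8-3-3 (1) describes an ELISA titration against two antigens. Positivity has a cut-off: "An IgG titer exceeding the mean of ELISA absorbance + 3 S.D. in healthy human serum is defined as positive". Change has none: an increase or decrease "is defined as a change in the maximum dilution fold that shows positive results". The section gives no dilution series, minimum fold change, replicate or confirmation, and it does not ask for baseline and later sera to be tested together.

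Section 9-4-1 sets the sampling: "Blood samples will be drawn at baseline, every 4 weeks after 5, 9, and 12 weeks if possible". Read with the heading of that section, this gives up to three post-baseline comparisons by Week 12 for each of two antigens.

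Section 11-4 places the antibody response under efficacy, with the instruction "To be investigated in an exploratory manner for each treatment group". It is not among the primary or secondary endpoints in 8-1 and 8-2.

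The antibody test also appears in the maintenance criterion. Section 7-8 item 2 refers to "SD or greater in regulatory T-cell elimination and antigen-specific antibody immunoreactivity or RECIST". Section 7 of the summary has "regulatory T-cell clearance effect and antigen-specific antibody immunoreactivity or SD or better on RECIST after 8 doses", and section 9-1 is worded to the same effect. Section 7-1 (Phase Ib) instead lists the regulatory T-cell test, the antibody test and imaging as three alternatives.

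**The concern.** The mean + 3 SD cut-off protects a clearly seronegative patient from being called positive by chance. It does nothing for a patient who already has a titre. If that patient's true titre lies close to a dilution boundary, the reading can fall on either side of it from one run to the next, and the rule records each upward flip as an increase.

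Every group in the trial receives mogamulizumab, so no untreated arm shows how often this happens without drug. Reported increases by treatment group would mix true responses with flips. The exploratory comparison in 11-4 between regulatory T-cell elimination and antibody response would be blurred by the same misclassification.

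This is not a matter left to the SAP. The protocol itself fixes the definition, and an analysis plan would inherit it.

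**Working it through.** The protocol states no error rate for this item, so there is no figure to reproduce. The question is how often the stated rule calls an increase when nothing has changed.

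**Inputs from the protocol.** The rule is any step (8-3-3 (1)). Post-baseline visits are Weeks 5, 9 and 12 (9-4-1).

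**Assumed inputs, not in the protocol.**
- Dilution series of two-fold, four-fold or ten-fold, so the step width is h = 1, 2 or log2(10) = 3.322 log2 units.
- Assay SD σ = 0.25, 0.5 or 0.75 log2, normal and independent between visits.
- True titre stable, and equally likely to lie anywhere within a step.

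**Formula for one visit.** Let D be the follow-up error minus the baseline error, so D ~ N(0, 2σ²). Because the position within the step is uniform, the chance of at least one step up is

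P = E[min(max(D, 0)/h, 1)].

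When noise is small against the step, this is close to σ/(h√π) = 0.564 σ/h.

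- Two-fold, σ = 0.25: 0.564 × 0.25 / 1 = 0.141.
- Four-fold, σ = 0.25: 0.564 × 0.25 / 2 = 0.071.
- Ten-fold, σ = 0.25: 0.564 × 0.25 / 3.322 = 0.042.
- Ten-fold, σ = 0.75: 0.564 × 0.75 / 3.322 = 0.127.
- Two-fold, σ = 0.75: the approximation gives 0.423. Subtracting E[max(D − h, 0)]/h = 0.098 leaves 0.325.

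Simulation of the same model agrees with these values and gives the three-visit figures.

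| Series | σ (log2) | False increase, one visit | False increase at any of three visits |
|---|---|---|---|
| Two-fold | 0.25 / 0.5 / 0.75 | 14.1 / 25.7 / 32.5% | 26 / 45 / 55% |
| Four-fold | 0.25 / 0.5 / 0.75 | 7.1 / 14.1 / 20.5% | 13 / 26 / 37% |
| Ten-fold | 0.25 / 0.5 / 0.75 | 4.2 / 8.5 / 12.7% | 8 / 15 / 23% |

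All figures are for one antigen and for patients at or near a positive dilution. At a single visit, false decreases are equally likely by symmetry. The last column applies only if an increase at any visit is allowed to count, which the protocol does not say.

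**Effect of requiring two steps in a two-fold series.** At one visit the false-increase rate becomes less than 0.1%, 2.5% and about 9% for the three SDs. Over three visits it becomes about 0.1%, 6% and 19%.

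**Scale in patients.** The seropositive share of a Phase Ib group of 20 is not given. For every five such patients, the expected number of false increases at one visit for one antigen runs from 5 × 0.042 = 0.2 to 5 × 0.325 = 1.6.

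**The case against.** The item is exploratory. It sits under other items, outside the primary and secondary endpoints, and 8-3-2 bases the recommended dose on safety and regulatory T-cell elimination, not on antibody. This stands, and it limits the weight of the point.

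The rates depend on a dilution series, an assay SD and a seropositive share that the protocol does not give. This also stands: a coarse series brings the one-visit rate down to a few percent. It does not remove the defect, because a titre near a boundary can flip in any series. A clearly seronegative patient is hardly exposed, since chance crossing of mean + 3 SD is about 0.1% under normality. It would therefore be wrong to say that chance increases build up in every patient.

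Symmetric noise produces decreases as well, and reporting both would reveal some of it. That helps a careful reader of the tables but does not correct the classification of individual patients.

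Same-run pairing is often set in a laboratory procedure, so its absence alone would be no finding. It is part of the remedy here because the stated rule has no margin to absorb run-to-run variation.

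A reader might infer that a noisy one-step increase lets a patient continue dosing. The document does not support that. No maintenance passage uses the word increase, and immunoreactivity there could equally mean positivity. Section 7-8, section 7 of the summary and section 9-1 join the antibody result to the T-cell effect. Section 7-8 also requires the patient's wish and the investigator's judgement.

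**Conclusion.** The point holds in a limited form. As written, 8-3-3 (1) cannot separate a one-step flip from a real change in antibody. In patients at or near a positive titre, the false-increase rate at one visit for one antigen is about 14–33% with a two-fold series, 7–21% with a four-fold series and 4–13% with a ten-fold series. These rates assume a stable true titre and an assay SD of 0.25 to 0.75 log2. They rise if any of Weeks 5, 9 and 12 may count. What is affected is an exploratory result in a trial with no untreated group.

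The point does not extend to the primary or secondary endpoints or to the dose recommendation. It does not show that an increase satisfies the maintenance criterion. What can be said about maintenance is narrower: section 7 of the summary, 7-1, 7-8 and 9-1 disagree on how the antibody result enters, and none says what result meets it.

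**What to change.** In 8-3-3 (1):

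- State the dilution series.
- Define an increase or decrease as a change from baseline larger than one-step assay variation, for example at least two steps in a two-fold series (four-fold). The number of steps should follow from the series and the assay's precision, because two steps in a four-fold series would already be sixteen-fold.
- Have each patient's baseline and follow-up sera assayed in the same run.
- Continue to list raw titres.

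The cost is a few lines of text and batch planning at the external laboratory. The downside is that small true changes will not be classified as changes, although the listed titres will still show them.

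Separately, the sponsor must reconcile section 7 of the summary, 7-1, 7-8 and 9-1 on how the antibody result enters the maintenance criterion, and state what antigen-specific antibody immunoreactivity means there. No threshold for that criterion is proposed here.

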**9. Observation items and methods**

**9-1. Clinical trial schedule**

The prescribed observations and examinations will be conducted according to the following schedule1. Patients will be hospitalized from before the first administration to the day after the first administration.

For subjects in Phase Ia, the investigators will obtain consent for the continuation of the clinical trial again prior to the 5th administration.

After 8 doses, if the subject has shown a regulatory T-cell elimination effect and antigen-specific antibody immunoreactivity or SD or higher on RECIST, the investigator may continue to administer the investigational drug if the subject wishes to receive maintenance dosing and the investigator determines that maintenance dosing is appropriate.

The first dose of investigational drug is defined as 1 week.

[figure not shown]
Table 1. Clinical trial schedule

○：Additional items to be performed when maintenance dosing is performed after 8 doses.

*1: The ninth and subsequent doses of the investigational drug should be administered only when SD or better is confirmed in the regulatory T-cell elimination effect and antigen-specific antibody immunoreactivity or RECIST, the subject wishes to receive a maintenance dose of the investigational drug, and the investigator and others consider that the maintenance dose of the investigational drug is appropriate.

*2: Continuous observation from before the start to the end of study drug administration.

*3: To be conducted before administration of the investigational medicinal product during the period of administration of the investigational medicinal product.

*4: Before administration of the investigational drug, at 30 minutes, 1 hour, 1.5 hours after the start of administration, at the end of administration, 30 minutes and 1 hour after the end of administration.

*5: If it is difficult to collect the prescribed volume of blood due to signs of anemia, etc., the following tests should be performed in consideration of subject safety: 1. General blood test (facility prescribed volume), 2. Thyroid function test (facility prescribed volume), 3. Regulatory T cell test (10 mL), 4. Pharmacokinetic test (Phase Ia part only, 2 mL), 5. Antigen-specific antibody immunological reaction test (5mL), 6. Genetic analysis (15mL), 7. Immunopotentiation effect test (30~50mL), 8. Tumor markers (facility's specified volume), as much blood as possible in the order of priority.

*6: Testing is also performed at week 12 after the last dose of the study drug.

*7: The volume of blood drawn per dose should be 2 mL. See Table 2 for the timing of the test.

*8: The test items should be those indicated in (2), (4) to (6) of 8-3-3 Definition of other items.

*9: Blood sampling on multiple days is acceptable.

*10: Adverse events should be observed until 12 weeks after the last dose of the study drug. However, for non-hematological toxicities of Grade 3 and above, the observation period for adverse events is up to 24 weeks.

*11: If no maintenance dose is given after 8 doses and the study is discontinued after 12 weeks of testing, only general blood tests, CT or MRI, antigen-specific antibody immunoreactivity tests, regulatory T-cell tests and immunoenhancing effect tests should be performed when the study is discontinued.

[figure not shown]
Table 2. Schedule of blood sampling for pharmacokinetic testing (only in phase Ia part)

**9-2. Patient background**

The following items should be verified and included in the case report form.

Date of obtaining consent, date of birth, gender, height, primary disease (name of primary disease, pathological or histological type, date of diagnosis, diagnostic method, TNM classification, staging), history of treatment for primary disease, medical history*, complications**, whether tumor antigen (NY-ESO-1, XAGE-1b) expression, HIV test***, HCV test***, HBs antigen test***, HBc antibody test***, HBs antibody test***, HBV-DNA test (performed if HBc or HBs antibody test result is positive)**, CCR4 expression test (IHC), arterial blood oxygen saturation, ECG, left heart ejection fraction, pregnancy test*** (hCG test: limited to premenopausal women)

*: Clinically problematic disease cured between 1 year prior to the start of the study drug and case enrollment, as well as any disease that was previously diagnosed more than 1 year prior to the start of the study but deemed important for the patient background.

**: Diseases that have not been cured at the time of case enrollment

***: To be conducted within 4 weeks prior to case enrollment.

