**1-3-1-2. Toxicity test**

Toxicity was evaluated using crab-eating macaques, in which antigen expression was observed in tissues similar to those of humans. As for acute toxicity, no deaths or changes in general condition were observed at doses up to 100 mg/kg, and the approximate lethal dose was considered to be 100 mg/kg or higher. No effects of the test substance were observed after repeated weekly dosing for up to 13 weeks, and the non-toxic dose was 40 mg/kg/week, the highest dose studied in this study. The AUC0-7d at the non-toxic dose was more than 33 times higher than the AUC0-7d value at 8 doses of 1 mg/kg in the clinical study. In a study on embryo-fetal development, administration of 40 mg/kg/week to pregnant crab-eating macaques showed no general toxicity or reproductive effects in the mother. Furthermore, no effects on embryo-fetal development were observed, although there was some transfer of mogamulizumab to the fetus. In addition, no findings of local irritation were observed in the evaluation of the site of administration within each toxicity study.

Single and repeated administration studies in crab-eating macaques showed the production of anti-Mogamulizumab antibodies. Even in individuals that did produce anti-Mogamulizumab antibodies, there were no significant findings in toxicity studies, and anti-Mogamulizumab antibodies were not considered to pose a safety issue.

The decrease in CCR4-positive T cells observed in the toxicity study was based on the pharmacologic effects of mogamulizumab. In the single-dose study with a 12-month observation period, a recovery trend was observed, but the levels remained low throughout the observation period; in the 4-week repeat-dose study, a recovery trend was observed after approximately a 3-month withdrawal period, but the levels remained low at the last examination. However, no signs of toxicity were observed in either study, and the persistent decrease in CCR4-positive T cells was considered not to be a concern for developing toxicity.

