**4-1. Selection criteria for patients**

Patients with advanced or recurrent solid tumors who meet all of the following criteria at the time of enrollment will be eligible.

1) Patients whose tumor cells are negative for CCR4 expression (diagnosis should be made using a method commercialized in Japan) and whose histopathological diagnosis of malignancy such as lung cancer, gastric cancer, esophageal cancer, malignant melanoma, or ovarian cancer is confirmed.

2) Patients who are refractory or intolerant to standard treatment, have no appropriate treatment, or have refused standard treatment.

3) Patients with a performance status (ECOG criteria) of 0, 1, or 2

4) Patients must be at least 20 years of age on the date of obtaining consent to participate in the clinical trial.

5) No severe damage to major organs (bone marrow, heart, lungs, liver, kidney, etc.) and laboratory values (within 2 weeks prior to enrollment) that meet the following criteria

Neutrophil count: 1,500/μL or more

Hemoglobin level: 8.0 g/dL or higher

Platelet count: 75,000/μL or higher

Serum total bilirubin level: 2.0 mg/dL or less

AST (GOT), ALT (GPT): not more than 2.5 times the upper limit of the facility standard (not more than 5.0 times the upper limit of the facility standard if the cause is judged to be hepatic infiltration due to the primary disease)

Serum creatinine: 1.5 mg/dL or less

Arterial blood oxygen saturation: 93% or higher (room temperature)

Electrocardiogram: No abnormal findings requiring treatment

Left heart ejection fraction (by echocardiography): 50% or more

6) The patient must agree to use a condom or other contraceptive method from the time of consent until 24 weeks after completion of study drug administration (excluding postmenopausal women (more than 1 year after the last menstrual period) or women who have undergone surgical sterilization and men who have undergone surgical sterilization)

7) The patient has given written consent.

8) Patients who are able to be hospitalized for the administration of Mogamulizumab from before the first dose until the day after the first dose.

9) Patients with measurable lesions in RECIST ver. 1.1 (New response evaluation criteria in solid tumours:Revised RECIST guideline (version 1.1)^12)^. Patients must have measurable disease at

10) Expected survival of at least 3 months.

<Rationale for setting>

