**4-2. Exclusion criteria for patients**

Patients who meet any of the following criteria at the time of enrollment will be excluded.

1) HIV antibody-positive cases

2) HCV antibody positive

3) Patients with autoimmune diseases

4) Patients who are reported to be HBs antigen positive or HBV-DNA "detected" by real-time PCR

5) Patients with a history of serious hypersensitivity to the administration of antibody products

6) Patients with multiple cancers. However, overlapping cancers are defined as simultaneous overlapping cancers and iatrogenic overlapping cancers with a disease-free period of 5 years or less. Carcinoma in situ (intraepithelial carcinoma) or intramucosal carcinoma that is considered curable by local treatment is not included in overlapping cancers.

7) More than 4 weeks have not elapsed from the scheduled start date of the study drug administration since the administration of anticancer agents, continuous systemic administration of corticosteroids, immunosuppressive or immunoenhancing agents, cytokine therapy, radiation therapy, or surgery for the primary disease.

8) Pregnant, lactating, or possibly pregnant patients

9) Patients with active infectious diseases

10) Patients with psychiatric disorders or dementia

11) Patients requiring continued treatment with systemic steroids

12) Patients undergoing transplantation therapy such as hematopoietic stem cell transplantation

13) Patients with central nervous system tumor invasion or with clinical findings that suggest such invasion

14) Patients who received other investigational drugs within 4 weeks of case enrollment

15) Patients who have received immunotherapy (e.g., tumor vaccine) within 12 weeks of case enrollment

16) Other patients who are considered to be inappropriate for the clinical trial

<Rationale for setting>

1), 2), 4) The above values were determined in consideration of safety and the safety of those who handle blood and other specimens.

3) The investigational drug may cause exacerbation of autoimmune diseases.

5), 8), and 9) The safety of the study subjects could not be ensured.

6) The dose was set because of the possibility of affecting safety and life prognosis.

7) The efficacy evaluation may be affected.

10) The reason for exclusion of patients who have difficulty in obtaining appropriate consent.

11) The inclusion criteria were established because of the possibility of influencing the evaluation of the investigational drug.

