**7-5. Method of enrolment and allocation**

**7-5-1. Procedure for enrolment of subjects**

After receiving approval from the Clinical Trial Review Committee and submitting the clinical trial plan, the investigators at each site obtain consent in writing after providing sufficient explanation to the candidate cases, conduct necessary tests to determine eligibility, and request case registration to the Case Registration Center. The case registration center will determine the eligibility of the cases, assign a designated registration number only to subjects who are determined to be eligible, and report the results to the principal investigator, etc. via fax.

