**7-7. Dosing methods**

When administering the drug, ensure that the drug meets the "7-7-1. Administration Criteria" and does not conflict with the "7-7-2. Postponement of Administration Criteria" and "7-7-3. Criteria for discontinuation of administration”.

The investigational drug must be started within 2 weeks of case enrollment.

[Phase Ia] Either 0.1 mg/kg, 0.5 mg/kg or 1.0 mg/kg dose is administered intravenously over 2 hours once a week for a total of 8 doses.

[Phase Ib] If tolerability up to 1.0 mg/kg was confirmed in Phase Ia, 0.1 mg/kg or 1.0 mg/kg18

or 0.1 mg/kg or 0.5 mg/kg if tolerability up to 0.5 mg/kg is confirmed, or 0.1 mg/kg if tolerability up to 0.1 mg/kg is confirmed, administered intravenously over 2 hours once a week for a total of 8 doses.

[Common to both Phase Ia and Phase Ib]

1) Maintenance dose

The ninth and subsequent doses of the investigational drug will be administered every 4 weeks as maintenance doses, provided that "7-8. Criteria for Drug Discontinuation" are not violated.

2) Dosing Interval

The dosing interval should not be shortened until 8 doses have been administered. After the 9th dose, dosing may be postponed for up to 2 weeks, and the next dose may be shortened by up to 2 weeks.

3) Pre-treatment at the time of administration

Since reactions associated with injection are expected to occur in almost all patients, 30 to 50 mg of diphenhydramine and 300 to 500 mg of acetaminophen should be taken 30 minutes prior to administration of the study drug. In addition, 100 mg of hydrocortisone should be administered intravenously before the second dose of diphenhydramine 30-50 mg and 300-500 mg of acetaminophen after the first dose. Dosage may be adjusted according to age and symptoms.

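### The pregnancy test is tied to enrolment rather than to first dose, so a negative hCG can be 42 days old at the first infusion

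*Protocol*

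**What the plan says.** Section 9-2 lists the pregnancy test (hCG, premenopausal women only) among the patient background items. It carries the same footnote as the HIV, HCV and hepatitis B tests: "To be conducted within 4 weeks prior to case enrollment".

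Section 7-7 sets the interval that follows: "The investigational drug must be started within 2 weeks of case enrollment".

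Section 4-1, item 5, sets a shorter window for the organ-function criteria: "laboratory values (within 2 weeks prior to enrollment) that meet the following criteria".

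Three other provisions bear on the risk:

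- Section 4-1, item 6, on contraception, says that each participant "must agree to use a condom or other contraceptive method from the time of consent until 24 weeks after completion of study drug administration".
- Section 7-5-1: investigators "obtain consent in writing after providing sufficient explanation to the candidate cases, conduct necessary tests to determine eligibility, and request case registration", in that order.
- Section 4-2, item 8, excludes "Pregnant, lactating, or possibly pregnant patients". The lead-in fixes when this is judged: "Patients who meet any of the following criteria at the time of enrollment will be excluded".

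Section 10-6 says what happens once a pregnancy is known: dosing stops and the pregnancy is reported and followed up.

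**The concern.** A 4-week window suits serology, which seldom changes over a few weeks. Pregnancy status can change within that time, and a test taken very early in a pregnancy can be negative. What matters for fetal exposure is the patient's status at the first infusion, yet the test is timed to enrolment, which can be two weeks earlier.

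The protocol gives its own reasons for caution. The rationale for the contraception criterion in section 4-1 is that safety for the fetus is not established. Section 1-3-1-3 reports that the drug reached the fetus in pregnant macaques. Section 10-6 acts only after a pregnancy has been recognised, which may be after exposure.

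Two cases remain open: a pregnancy too early for the screening test to detect, and a contraceptive failure between that test and dose 1. No endpoint, dose decision or analysis is affected; this is a question of patient safety.

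**Working it through.** The protocol states no maximum test age at first dose, so there is no figure to reproduce. The check adds two time windows.

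**Inputs**

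- Earliest hCG test: 4 weeks = 28 days before enrolment (section 9-2).
- Earliest eligibility laboratory values: 2 weeks = 14 days before enrolment (section 4-1, item 5).
- Latest first dose: 2 weeks = 14 days after enrolment (section 7-7). The postponement rule in 7-7-2 does not lengthen this, because 7-7 caps the start of dosing.

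**Formula:** maximum age at dose 1 = maximum days from test to enrolment + maximum days from enrolment to dose 1.

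- hCG: 28 + 14 = **42 days**.
- Eligibility laboratory values: 14 + 14 = **28 days**.
- Difference: 42 − 28 = 14 days. Ratio: 42 / 28 = 1.5.

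**Is there a repeat test in the readable text?** I looked wherever one would be expected.

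- Dosing and deferral criteria (7-7-1, 7-7-2): pregnancy is not mentioned.
- General blood tests (9-5-4): repeated before each dose, but hCG is not among the items.
- Thyroid tests and urinalysis (9-5-5, 9-5-6): hCG is not among the items.
- Footnotes to Table 1 (9-1): no mention. The footnote that ranks blood tests by priority names eight, none of them hCG.
- Visit windows (11-3): thirteen scheduled items, including the baseline-only gene analysis; no pregnancy test.

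The body of Table 1 is not legible, so a repeat that appears only there cannot be ruled out.

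**Effect of the fix at dose 1:** with a 3-day window the maximum falls from 42 to 3 days, a reduction of 39 days.

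**Limit of the fix at dose 8:** without postponement, dose 8 comes 7 weekly intervals, or 49 days, after dose 1. The last required result could then be 42 + 49 = 91 days old under the present text and 3 + 49 = 52 days old with the fix.

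**Number of patients:** planned enrolment is at most 18 + 40 = 58, both sexes together (section 7-6). The number of premenopausal women is not given, so no expected count of affected patients can be calculated.

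**The case against.** The strongest objection is that the schedule itself cannot be read. A pre-dose hCG is just the sort of item Table 1 might hold, and a table lost in reproduction is not a gap in the plan. This stands as a condition on the finding. Against it, section 9 describes the repeated tests in text, whereas the pregnancy test appears only under patient background.

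Second, nothing is contradictory. The two windows are compatible, and timing a screening test to enrolment is a design choice. That is true, and it is why the point is offered as an improvement and not as an error.

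Third, the 28-day comparison says little about risk. Blood counts and biochemistry are repeated before every dose, and 7-7-1 allows results at most 3 days old, so in practice those values are fresher than 28 days at dose 1. This is correct, and the 1.5-fold ratio should carry no weight. But it makes the hCG test stand out more: other safety laboratory values are renewed before dosing, and no readable text renews this one.

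Fourth, the risk is already reduced in several ways. Consent, and with it contraception, comes before the eligibility tests. The exclusion of possibly pregnant patients is judged at enrolment, at most 14 days before dose 1. The investigator may postpone any dose (7-7-2) and must stop dosing in a patient found ineligible (7-7-3). Macaques given 40 mg/kg/week showed no embryo-fetal effect, and on the margin at that dose section 1-3-1-2 says: "The AUC0-7d at the non-toxic dose was more than 33 times higher than the AUC0-7d value at 8 doses of 1 mg/kg". All of this stands and makes the residual risk small. It does not remove it: a condom alone satisfies the contraception criterion, and the judgement at enrolment may rest on a test 28 days old.

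Finally, the fix covers dose 1 only, and a result could still be 52 days old at dose 8. This also stands. Later doses would continue to rely on contraception and section 10-6. A check before the first exposure is still worth having, because at that point exposure can be avoided altogether.

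**Conclusion.** The concern holds. As the text reads, a negative pregnancy test can be up to 42 days old at the first infusion, and no readable provision requires a newer one. The 42 days is a worst case: test on the first permitted day, first dose on the last. It is neither a typical interval nor a count of pregnancies.

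The conclusion rests on one assumption, that Table 1 does not schedule a repeat hCG before dose 1. If it does, the concern falls away. Given the existing safeguards and the macaque data, the residual risk is small and cannot be quantified from the protocol. Confidence is medium, and the point is one to consider.

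**What to change.** Give the pregnancy test its own footnote in section 9-2, tied to first dose. Keep the enrolment test as it is, and add that premenopausal women need a negative hCG before the first infusion, either on the pre-dose blood sample of section 9-5-4 or within the 3 days before dosing, the window already used in note *3 of section 7-7-1. If Table 1 already schedules such a test, only the footnote in 9-2 needs to be brought into line with it.

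The cost is one extra assay per premenopausal woman, on blood that is drawn anyway, in patients who are already in hospital before the first dose (section 9-1). Rarely, an enrolled patient would be found pregnant before dosing and would have to be replaced.
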